### Follow-up

Follow-up visits among all postoperative patients will be regularly accomplished. The schedule consists of physical examinations, laboratory tests and imaging examinations. Laboratory examinations contain routine blood tests and assessment of tumor biomarkers including CEA, AFP, CA19–9, CA125 and CA153. Imaging examinations (CT, enhanced CT, MRI or PET-CT) will also be performed regularly. Gastroscopy will be done once annually. The follow-up will be performed every 3–6 months for the first 2 years after the operation and every 6–12 months for the following years, according to the schedule (Table 1). Each participant will be tracked for at least 3 years, or until he or she suffers a loss or dies.

**Table 1 Tab1:** Checklist for collection of necessary clinical data and follow-up schedule of enrolled patients

	Baseline information			Follow-up (months)							
	Preoperation	Operation	Discharge	1	3	6	12	18	24	30	36
Informed consent	**√**										
Demographic information	**√**										
Anamnesis	**√**			**√**	**√**	**√**	**√**	**√**	**√**	**√**	**√**
Oncology history	**√**										
Biopsy	**√**										
Tumor classification	**√**										
Laboratory tests	**√**			**√**	**√**	**√**	**√**	**√**	**√**	**√**	**√**
Physical examination	**√**			**√**	**√**	**√**	**√**	**√**	**√**	**√**	**√**
Inclusion/Exclusion	**√**										
Randomization	**√**										
Postoperative Complication				**√**							
Pathology			**√**								
Chest X-ray/CT	**√**						**√**		**√**		**√**
Gastroscopy	**√**						**√**		**√**		**√**
Abdominal CT/MRI	**√**				**√**	**√**	**√**	**√**	**√**	**√**	**√**
Abdominal ultrasound					**√**	**√**	**√**	**√**	**√**	**√**	**√**
Concomitant Medication	**√**		**√**	**√**	**√**	**√**	**√**	**√**	**√**	**√**	**√**
Surgical information		**√**									

√: Indicates the need to collect the clinical data

This trial began on December 11, 2019. Enrollment will take about 3 years. The follow-up begins when the first patient completes the operation and ends when the last registered patient completes the postoperative 3-year follow-up.

### Data collection and management

When a patient is included in the study, a randomized number will be generated and applied in the database. The patient’s codes are accessible to PI and COI. The study coordinator will collect the clinical data and record it on a unique clinical case report form. Each center assigns a dedicated person responsible for the randomization of the enrolled patients, data entry, proofreading, uploading, etc. The final data is summarized in the central database. Data quality inspectors will regularly inspect and control the quality of data entry and database management.

### Intervention

Depending on randomization results, patients will undergo either the TH or the RTA approach operation. The technical details of both approaches are determined based on the preferences of individual surgeons, on the condition of achieving the key goal of completely tumor resection. Minimally invasive surgery and robotic surgery are allowed if the technology and equipment at the local research center are supported. However, if the tumor cannot be completely removed, the surgeons should promptly change their surgical strategy.

Proximal or total gastrectomy with standard D2 lymphadenectomy will be achieved by the transabdominal approach in the TH group. Distal esophagectomy and mediastinal lymphadenectomy will be done through the transhiatal approach. In the RTA group, the intra-abdominal procedure is the same as in the TH group. In addition, an oblique incision over the right thorax will be made, and esophagectomy and mediastinal lymphadenectomy will be completed through the right transthoracic approach.

Reconstruction methods should be determined by the attending physician based on experience and patients’ individual conditions during the operation. Proximal gastrectomy can be followed by gastric tube construction and esophagogastrostomy. It is recommended that the Roux-en-Y (esophagojejunostomy and jejunojejunostomy) reconstruction will be done following the total gastrectomy.

### Management and quality control

The surgeons participating in this study must meet the following conditions. Each surgeon must have performed the TH and RTA methods in at least 20 cases of AEG surgery and must have passed the qualification examination conducted by three experts in gastrointestinal surgery. Surgeons who want to perform minimally invasive or robotic surgery must prove that they have achieved the operation more than 20 times in a fixed surgical team recently. For a smooth and successful clinical trial, the researchers in all participating institutions must be experts in gastrointestinal surgery to avoid learning curve bias, which is the reason for strict institution invitation and quality control procedures. The pathologist who evaluated the specimens is blind to the surgical approaches because the rate of R0-resection and the status of LNs are the main results of this trial. Patients will be informed of the surgery group they are assigned to. If the patients refuse, they will accept the standard treatment plan of the relevant department.

Throughout the trial, ongoing surgical quality assurance will be undertaken. During each operation, photographs of the surgical details, including the lymphadenectomy region and the fresh specimens following the procedure, will be taken. As a result, these pictures will be used for constant feedback to validate the rationale of the surgical approach, the quality and adequacy of the lymphadenectomy and the integrity of the specimens. They will also be utilized by the research committees to examine and monitor the operation’s quality.

### Perioperative treatment

Nutritional support before surgery will be permitted for patients with nutritional risk followed by the Nutrition Risk Screening 2002 (NRS-2002 > 4). During the perioperative period, antibiotics will be used preventively following relevant national regulations. Postoperative preventive continuous intravenous analgesia will be allowed but is not mandatory. Postoperative fluid rehydration and nutritional support will be implemented based on the experience and rules of the physicians of each participating institution.

### Postoperative adjuvant treatment

Postoperative adjuvant chemotherapy will be principally advised for patients with pathologically confirmed as advanced AEG. The regimen will comply with the Japanese Gastric Cancer Treatment Guidelines 2018 (5th edition) [26].

### Outcome measurements

The primary endpoint of the study is the 3-year DFS. DFS is the timeframe between the operation and recurrence, progression, or death.

The secondary endpoint:3-year overall survival (OS): OS is the time from operation to death due to any cause or the last follow-up.R0-resection: Patients who undergo radical resection without positive margins;Number and station of lymph nodes (LNs): Detected in postoperative specimens;Postoperative mortality: Death within 30 days after surgery;Duration of postoperative hospitalization: The time from the operation to discharge;Postoperative complications: Postoperative complications include respiratory complications (postoperative pneumonia, pleural effusion, pulmonary insufficiency), cardiac complications (acute myocardial infarction, heart failure, arrhythmia), intra-abdominal bleeding, intra-abdominal abscess, anastomotic structure, anastomotic leakage, chyle leakage, deep venous thrombosis, and wound infection. All postoperative complications will be classified according to the Clavien-Dindo grading system [27];Quality of life (QOL): Using the European Organization for Research and Treatment of Cancer Quality of Life questionnaire (EORTC: QLQ-C30, QLQ-STO22, and QLQ-OG25 after 3, 6, 9, 12, 18, 24, and 36 months).

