### Study design

S2AEG is designed as a prospective, multicenter, randomized, open, and parallel controlled study conducted in China. This trial is funded by the Program for the Bethune Charitable Foundation (2019–12) and has been registered on Clinical-Trial.gov (NCT04910789, named S2AEG). All the Institutional Ethics Review Committees of participating research centers have approved this protocol. Any amendments that may affect the trial will be further communicated to obtain approval among the Institutional Ethics Review Committees. All researchers will conduct this trial in line with the Declaration of Helsinki and Good Clinical Practice guidelines. Before recruitment, each participant will provide written informed consent for the acquisition and use of anonymized clinical data. This study will be conducted by surgeons who are competent in performing both approaches. None of the patients, surgeons, or data analysts will be blinded.

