### Study population

The clinical efficacy of the TH and RTA approaches for the resectable ST-II AGE, which is the aim of the study. The eligibility of all patients will be determined by their surgeon.

The inclusion criteria are described briefly below:Aged 18–75;Histologically confirmed as Siewert type II AEG;Clinical stage ranges cT1-4aN0-3 M0 (According to the 8th AJCC TNM staging system) and is confirmed by the preoperative examinations (Gastroscopy, enhanced or not computer tomography (CT), magnetic resonance imaging (MRI) or positron emission tomography with CT (PET-CT)).The operation will be performed by either TH or RTA approach according to the direction of the research center and the surgeon;American Society of Anesthesiologists (ASA) physical status score of 1–3;Eastern Cooperative Oncology Group (ECOG) performance status of 0–1;Laboratory test criteria: hemoglobin > 90 g/L, white blood cell > 3 × 10^9/L, platelets > 100 × 10^^9^/L, serum albumin (ALB) > 30 g/L, renal function (serum creatinine (Scr) < 1.5 × ULN and glomerular filtration rate > 60 ml/min), and liver function (alanine transaminase (ALT) and aspartate transaminase (AST) less than 2.5× upper limit of normal);Informed consent of patients is required.

The exclusion criteria are as follows:Siewert type I or III AEG;Postoperative pathological types confirmed as non-adenocarcinoma or non-simple adenocarcinoma;Distant metastasis (M1) or invasion of the peritoneum;Clinically significant central nervous system disease that may influence compliance;Clinically significant diseases (Irregularly controlled diabetes and hypertension; History of myocardial infarction or cerebral infarction within 6 months before the operation; Heart function: New York Heart Association (NYHA) class II or higher; Respiratory function: Forced expiratory volume in the first second (FEV1) < 50%; Liver function: Child-Pugh class C; Renal function: Serum creatinine (Scr) > 1.5xULN and glomerular filtration rate < 60 ml/min;History of gastrectomy (including endoscopic mucosal resection or submucosal dissection);Diagnosed with other malignancies within 5 years;Pregnancy or breast-feeding;Tumor-related complications (dysphagia, gastrointestinal bleeding, perforation, obstruction, etc.) requiring emergency surgery;Being assessed by the investigator as unsuitable for the trial;Persistent withdrawal from clinical trials.

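### DFS and OS are timed from the operation, not from randomisation, so a randomised patient who is never operated on has no start date; one exclusion also acts after allocation

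*Protocol article*

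**What the plan says.** All references are to the protocol article.

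- **Inclusion and randomization of patients:** eligibility is checked, patients are allocated 1:1, and surgery follows within a week.
- **Outcome measurements:** for the primary endpoint, "DFS is the timeframe between the operation and recurrence, progression, or death". For overall survival, "OS is the time from operation to death due to any cause or the last follow-up".
- **Follow-up:** "Follow-up visits among all postoperative patients will be regularly accomplished", and at trial level "The follow-up begins when the first patient completes the operation". The same section also says that every participant is to be followed for three years or more unless lost or dead.
- **Management and quality control:** patients learn their allocation, and "If the patients refuse, they will accept the standard treatment plan of the relevant department". The pathologist is blinded to the approach.
- **Study population:** the exclusion list contains "Postoperative pathological types confirmed as non-adenocarcinoma or non-simple adenocarcinoma", although histological confirmation is already an inclusion criterion.
- **Statistical analysis:** Kaplan–Meier curves and a log-rank test compare the groups. The section does not say which patients make up the groups. An article commonly leaves that to a fuller document, so the silence alone is not a finding.

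**The concern.** Randomisation makes the two arms comparable at the moment of allocation. That comparability carries through to the primary result only if every allocated patient can contribute an outcome. Here the endpoint needs a later event, the operation, and whether it takes place can depend on the arm. Allocation is open, refusal is foreseen, and the Background section reports more complications and longer stays with the thoracoabdominal approach. Unequal refusal or non-operation between TH and RTA is therefore plausible, though nothing in the article shows it.

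The length of the delay is not the issue. The issue is who has no clock at all. A later analysis plan could name an intention-to-treat set, but it would then meet an endpoint that is undefined for some of its members. If those patients had not been visited, their outcomes could not be recovered at analysis. The postoperative histology criterion is a second, smaller route by which patients leave after allocation.

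**Working it through.** The plan gives no figure of its own on this point, so there is none to reproduce. The check applies the stated rules to each kind of randomised patient and then illustrates the possible size.

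**Step 1: who has an endpoint under the stated rules**

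| Randomised patient | Start date for DFS/OS | What the article says about keeping the patient |
|---|---|---|
| Operated on as assigned | Yes, up to a week after randomisation | Followed |
| Refuses the arm, operated on by another route | Yes | Receives departmental treatment; arm for analysis not stated |
| Refuses or becomes unfit and is never operated on, or dies before surgery | None | Unclear: visits are for operated patients, yet every participant is to be tracked |
| Operated on, other histology found | Yes | Meets an exclusion criterion after allocation |
| Approach changed during surgery | Yes | No statement that the patient is dropped or moved |

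The third row is the defect in the endpoint definition. The fourth is the post-allocation exclusion.

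**Step 2: the clock shift itself**

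At most 7 days in 3 years: 7 / (3 × 365.25) = 0.6%. This is negligible.

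**Step 3: illustration of loss from one arm**

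Inputs from Sample size calculation: 3-year DFS 41.5%, planned difference 0.07. Assumptions, not in the documents: f, the share of an arm lost, and d, the gap in 3-year DFS between patients retained and lost.

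If retained patients have DFS x, the whole arm has (1 − f)x + f(x − d) = x − fd. The retained group therefore overstates its arm by fd. The bias in the difference between arms is f₁d₁ − f₂d₂.

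- 10% lost from one arm, none from the other, gap 20 points: 0.10 × 20 = 2.0 points, and 2.0 / 7 = 29% of the planned difference.
- Low end, 5% and 10 points: 0.05 × 10 = 0.5 points.
- High end, 15% and 30 points: 0.15 × 30 = 4.5 points.
- Same f and d in both arms: 0.

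**Step 4: a second parameterisation**

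Suppose true DFS is 41.5% in both arms and the lost patients have DFS q. Retained patients then show (0.415 − fq)/(1 − f).

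- 10% lost from one arm only, q = 20%: (0.415 − 0.020)/0.90 = 43.9%, a false difference of 2.4 points.
- 10% lost from one arm only, q = 0: 0.415/0.90 = 46.1%, a false difference of 4.6 points.
- 10% against 2% lost, q from 20% down to 0: 2.0 to 3.8 points.
- 5% against none, q from 20% down to 0: 1.1 to 2.2 points.
- Equal loss in both arms: 0.

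With 156 randomised per arm, a two-sided 5% Wald test would have a true type I error of 7% (2.4-point case) to 13% (4.6-point case).

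**The case against.** The strongest reply is that the text shows little actual loss. Much of it stands.

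- A reader might infer that only operated patients are followed. The Follow-up section also says every participant is tracked, so the text is ambiguous, not exclusive.
- A reader might infer that refusers are dropped. The article says only which treatment they receive, and a refuser who is operated on still has a DFS time.
- A reader might infer that patients whose approach is changed are reassigned. "if the tumor cannot be completely removed, the surgeons should promptly change their surgical strategy" concerns conduct in theatre and says nothing about analysis.
- A reader might infer that exclusions are decided by people who know the arm. For histology the article says the opposite: the pathologist is blinded. With confirmation before entry, few cases should be affected.
- The withdrawal item in the exclusion list is unclear English. Reading it as removal after randomisation is only one interpretation.
- "None of the patients, surgeons, or data analysts will be blinded" is a disclosed open-label feature and does not decide which patients are compared. How to date an event when disease remains after surgery is also a separate question, and progression is already among the DFS events.

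The size calculation also depends entirely on assumed rates and on loss that differs between arms.

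What the reply does not remove is the stated time origin. Even if every participant is tracked, a patient without an operation has no DFS or OS as defined. Nor does blinding the pathologist alter the fact that a postoperative criterion acts after allocation.

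**Conclusion.** The concern holds in a limited form. The article fixes a time origin that some randomised patients may never reach, and it lists one exclusion that can be applied only after surgery. These are stated rules, not details left to another document. If non-operation or exclusion differs between arms, the primary comparison is no longer fully one of the randomised groups.

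The article does not support the stronger conclusion that the comparison is already not of the randomised groups. It gives no rate of refusal, non-operation or histological exclusion, so neither the size nor the direction of any bias is known. The figure of about 2 points (range 0.5 to 4.5) assumes loss of 5% to 15% from one arm, none from the other, and a gap of 10 to 30 points in 3-year DFS. Equal loss of similar patients would leave the difference unbiased.

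**What to change.** - **Outcome measurements:** define DFS and OS from the date of randomisation. Progression and death are already DFS events, so a patient who is not operated on can then be counted.
- **Follow-up and Statistical analysis:** state that all randomised patients are followed on the same schedule and analysed in the assigned arm, including those who refuse, are not operated on or change approach. This also settles the ambiguity between postoperative patients and every participant.
- **Study population:** take the postoperative histology criterion out of the exclusion list and use it to define a sensitivity analysis.
- **Per-protocol analysis:** keep one alongside and give it real weight. The Objective and Discussion sections expect TH to match RTA, and crossovers pull an as-randomised comparison towards no difference.

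The cost is a change of wording and follow-up of what should be a few patients who are not operated on. The as-randomised estimate will be somewhat diluted by crossovers. No treatment changes.

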### Sample size calculation

Following previous studies, the rate of 3-year DFS for AEG patients who underwent surgical treatment is about 41.5% [9]. We assume that there is a significant difference of 0.07 between the TH and the RTA groups. After taking a 10% dropout rate into account, with the conventional 5% type I error (Both sides) and 80% statistical power, the results showed that 156 patients per arm are required. Therefore, 356 patients will be recruited for the study.

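### The stated inputs do not give 156 patients per arm: that number has about 22–25% power, not 80%, for a 7-point difference in 3-year DFS

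*Protocol article*

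**What the plan says.** The whole justification is in the protocol article, section Sample size calculation. It starts from a literature figure, that "the rate of 3-year DFS for AEG patients who underwent surgical treatment is about 41.5" per cent, and continues: "We assume that there is a significant difference of 0.07 between the TH and the RTA groups". Dropout is built in ("After taking a 10% dropout rate into account"), and the result is given as "with the conventional 5% type I error (Both sides) and 80% statistical power, the results showed that 156 patients per arm are required". The section then gives a recruitment total: "Therefore, 356 patients will be recruited for the study". The abstract gives 312, split 156 and 156.

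Outcome measurements makes 3-year DFS the primary endpoint. Statistical analysis compares survival by Kaplan–Meier curves and a two-sided log-rank test. The article does not say which arm the 41.5% belongs to or which way the difference runs, and it states no non-inferiority or equivalence margin.

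**The concern.** Near a rate of 40%, a 7-point difference is small, and detecting it with 80% power takes many hundreds of patients per arm. A figure of 156 is out of scale with that.

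This is the only sample size justification for the primary endpoint. The abstract, Objective and Discussion all expect the transhiatal approach to do about as well as the right thoracoabdominal one, so a non-significant result is the likely and expected outcome. A reader told that the trial had 80% power for 7 points would take such a result as good evidence against a 7-point DFS difference. With the real power, it would not be.

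**Working it through.** **Inputs (Sample size calculation).** Reference 3-year DFS p₁ = 0.415; difference 0.07, so p₂ = 0.485 or 0.345 (direction not stated, so both are shown); two-sided α = 0.05 (z = 1.960); power 80% (z = 0.8416); dropout 10%, already included in 156. Evaluable per arm: 156 × 0.9 = 140.4, about 140.

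**1. Attempt to reproduce 156 with two proportions, pooled variance under the null.**

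n = [1.960·√(2p̄(1−p̄)) + 0.8416·√(p₁(1−p₁)+p₂(1−p₂))]² / 0.07²

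- 41.5% vs 48.5%: p̄ = 0.45; (1.960 × 0.7036 + 0.8416 × 0.7018)² / 0.0049 = 791.7, so 792 per arm. With dropout, 791.7 / 0.9 = 879.7, so 880.
- 41.5% vs 34.5%: p̄ = 0.38; (1.960 × 0.6864 + 0.8416 × 0.6847)² / 0.0049 = 753.6, so 754 per arm. With dropout, 753.6 / 0.9 = 837.3, so 838.

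The unpooled formula gives 789 and 751, and the arcsine formula 792 and 753. The stated 156 is not reproduced.

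**2. Attempt with the log-rank test (Schoenfeld).** Under proportional hazards, HR = ln p₂ / ln p₁, and events = 4(1.960 + 0.8416)² / (ln HR)².

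- 48.5%: HR 0.823, 825 events.
- 34.5%: HR 1.210, 864 events.

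Both event counts exceed the number of patients, whether that is 312 or 356.

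**3. Power delivered for 7 points.** Two-proportion power is Φ{[0.07√n − 1.960√(2p̄(1−p̄))] / √(p₁(1−p₁)+p₂(1−p₂))}. For n = 140 and 48.5% this is Φ[(0.828 − 1.379) / 0.702] = Φ(−0.785) = 0.216. Log-rank power is Φ(|ln HR|·√D / 2 − 1.960), where D is the number of events. For n = 140 and 48.5%, D to 3 years is 280 × 0.55 = 154, giving 0.227.

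| Patients per arm | Two proportions | Log-rank, events to 3 years | Log-rank, follow-up 3–6 years* | Log-rank, event in every patient |
|---|---|---|---|---|
| 140 | 22–23% | 23–24% | 27–28% | 36–37% |
| 156 | 24–25% | 25–26% | 30–31% | 39–41% |
| 178 (half of 356) | 26–27% | 28–29% | 33–35% | 44–45% |

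Ranges cover both directions of the difference. *Assumes exponential DFS and uniform accrual over 3 years.

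**4. What 140 evaluable per arm can do.**

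- Solving the formulas for the difference at 80% power gives 15.6 to 16.7 points, across both directions and both variance forms. That is more than twice 7.
- The 95% confidence interval half-width at 41.5% in both arms is 1.960 × √(2 × 0.415 × 0.585 / 140) = 0.115. It is 0.113 to 0.116 if the arms differ by 7 points.

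**5. Other readings tried, patients per arm before dropout.**

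- One-sided 5% superiority: 594 to 624.
- Non-inferiority, margin 0.07, equal true rates: 778 at one-sided 2.5%, 613 at one-sided 5%.
- Equivalence by two one-sided tests, margin 0.07: 849.
- Non-inferiority, margin 0.07, a true advantage of 0.07, one-sided 5%: (1.645 + 0.8416)² × 0.49255 / 0.14² = 155.4, so 156.

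The last returns the printed number but not from the printed inputs. It needs a margin and a one-sided test the article does not state, and its 156 is before dropout (156 / 0.9 = 173.3, so 174).

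**The case against.** Four points can be made for the plan or against the way its error is sized.

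- **The test.** DFS is defined as a time to event and the named survival test is the log-rank, so a two-proportion figure may understate power. This stands in part. With follow-up beyond 3 years, power could be 27–31% under the stated assumptions, and a true 7-point difference would then be missed 69–73% of the time rather than 75–78%. The ceiling, with an event in every one of 312 patients, is 41%.
- **The role of 0.07.** The hypothesis is worded as equivalence, so 0.07 may be a mislabelled margin. The text does not settle this, but with equal true rates a margin of 0.07 needs 613 or more per arm.
- **The source of 156.** It may come from a design or difference that was misreported, or 0.07 may be a misprint. That is possible: 41.5% vs 58% gives 140.2 per arm unpooled, and 140.2 / 0.9 = 155.8. The pooled formula gives 143.0, however, and the non-inferiority case above also lands on 156. These coincidences do not show where the number came from.
- **The larger total.** Recruiting 356 would help slightly, but 178 per arm still gives only 26–35%. The conflict between 312 and 356 is a separate error.

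**Conclusion.** The point holds. As printed, the inputs and the result contradict each other by a factor of more than five (838 to 880 per arm against 156). With 140 to 156 patients per arm, power for a 7-point difference is 22–25% for 3-year DFS compared as a proportion and about 23–26% for a log-rank test to 3 years.

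The two-proportion figures rest only on the article's own inputs, taken in both directions. The log-rank figures add proportional hazards, and the longer follow-up figures add exponential DFS and uniform accrual. No assumption about follow-up reaches 80%. A fuller protocol or analysis plan might explain where 156 came from, but it could not make the printed statement true.

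**What to change.** Correct the paragraph in Sample size calculation in one of two ways.

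- If 0.07 is a misprint, or another design was used, print the difference, margin, sidedness and formula that actually gave 156, and say whether dropout is included.
- Otherwise, withdraw the claim of 80% power for 0.07 and state what the design delivers. For example: 156 patients per arm (about 140 evaluable after 10% dropout) give 80% power, two-sided 5%, for a difference of about 16 points in 3-year DFS and about 22% power for 7 points; the 95% confidence interval for the difference will be about ±11.5 points.

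The 16 points should be described as what the sample size allows, since the article gives no rationale for a difference of that size. The same edit should say whether 0.07 is a difference to detect or a margin, and settle the total at 312 or 356, because the power figures depend on it.

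The cost is one corrected paragraph and a protocol correction, with a less favourable power statement. No extra enrolment is needed for the correction.

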**Methods:**

A prospective, multicenter, open, randomized, and parallel controlled study named S2AEG will be conducted. Three hundred and twelve patients who match the inclusion criteria but not the exclusion criteria will be participating in the trial and randomly divided into the TH (156) and RTA (156) cohorts. The primary efficacy endpoint is the 3-year disease-free survival (DFS) following the operation. The rate of R0-resection, the number and site of lymph nodes infiltrated and dissected, postoperative complications, hospital days and life quality are the second endpoints.

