### Inclusion and randomization of patients

On the completion of the baseline assessment and clinical staging, the criteria for inclusion and exclusion will be validated. Informed consent of all participants must be obtained in this trial. Subsequently, the participants will be further divided into the TH cohort or the RTA cohort in a ratio of 1:1 according to the computer-generated random numbers. Then these participants will receive the operation within 1 week after randomization.

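### The sample size section requires 156 patients per arm, which makes 312, but concludes that 356 will be recruited; the abstract says 312.

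*Protocol article*

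**What the plan says.** The size of the trial is given in two places in the protocol article.

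- **Abstract, Methods:** "Three hundred and twelve patients who match the inclusion criteria but not the exclusion criteria will be participating in the trial", and these are to be "randomly divided into the TH (156) and RTA (156) cohorts".
- **Sample size calculation:** "After taking a 10% dropout rate into account", with a two-sided 5% type I error and 80% power, "the results showed that 156 patients per arm are required". The next sentence reads: "Therefore, 356 patients will be recruited for the study".

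The section on inclusion and randomization fixes allocation "in a ratio of 1:1 according to the computer-generated random numbers". The Follow-up section expects enrolment to take about 3 years and ends follow-up when the last registered patient has completed 3 years after surgery. Nothing in the article mentions a screening allowance, a further dropout allowance or a third group.

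**The concern.** The total of 356 is presented as the consequence of the per-arm figure in the sentence before it, and it does not follow from that figure. It also disagrees with the abstract. The sample size section is where a reader looks for the target, and the total printed there is the one that its own calculation does not support.

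Two things depend on the number. The first is the recruitment target: if the trial closes at 312, a reader of the sample size section will think it stopped 44 short; if it closes at 356, a reader of the abstract will think it was extended. The second is the end of the study, because follow-up runs for 3 years from the last patient's operation, so a later last patient means a later completion date.

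**Working it through.** **Inputs.** Per-arm size 156, dropout of 10% already included, total 356, reference 3-year DFS 41.5%, difference 0.07, two-sided 5% and 80% power (Sample size calculation); total 312 as 156 + 156 (Abstract); 1:1 allocation (Inclusion and randomization of patients); enrolment of about 3 years (Follow-up).

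**Step 1: the total from the per-arm figure.** 2 x 156 = 312. This reproduces the abstract and does not reproduce 356.

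**Step 2: what 356 implies.** 356 / 2 = 178 per arm, a figure that the article does not contain. The gap is 356 - 312 = 44, and 44 / 312 = 14.1%.

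**Step 3: could 356 be a second dropout inflation?**

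| Method | Total |
|---|---|
| 312 x 1.1 | 343.2 |
| 2 x 172 (156 x 1.1 = 171.6, rounded up per arm) | 344 |
| 312 / 0.9 | 346.7, so 347 |
| 2 x 174 (156 / 0.9 = 173.3, rounded up per arm) | 348 |

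None gives 356. The nearest is 8 short, and this reading also contradicts the statement that the 156 already allows for dropout.

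**Step 4: accrual time.** Assume that 312 patients enter evenly over 36 months: 312 / 36 = 8.67 per month, and 44 / 8.67 = 5.1 months.

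**Step 5: power at either total.** Two-proportion normal approximation, two-sided 5%, no dropout, n per arm:

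power = Phi{ [d - 1.96 x sqrt(2 p(1-p)/n)] / sqrt([p1(1-p1) + p2(1-p2)]/n) }

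Here d = 0.07, p1 = 0.415 and p is the mean of p1 and p2. The direction of the difference is not stated, so p2 is taken as 0.485 and as 0.345.

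For n = 156 and p2 = 0.485: [0.07 - 1.96 x 0.05633] / 0.05619 = -0.719, so power is 23.6%.

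| n per arm | 41.5% vs 48.5% | 41.5% vs 34.5% |
|---|---|---|
| 156 | 23.6% | 24.6% |
| 178 | 26.3% | 27.4% |

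Using the unpooled variance throughout raises each figure by about 0.2 points (27.6% at most for 178), hence 24-25% and 26-28%. After 10% loss they fall to about 22% (140 evaluable per arm) and 24-25% (160 evaluable).

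**Step 6: what the stated inputs need.** For 80% power the same approximation requires 792 per arm before dropout (41.5% vs 48.5%) or 754 (41.5% vs 34.5%).

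**The case against.** The strongest reply is that this is a slip in one number. The abstract's total, the abstract's two arm sizes and the per-arm figure in the sample size section all agree on 312; only 356 stands alone. That is fair, and it is why 312 is the default in the fix. It does not dispose of the point, because the article does not show that 356 is the slip, and 356 is the number offered as the conclusion of the calculation.

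Three stronger readings are tempting and are not supported.

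- **That recruitment could stop anywhere between 312 and 356 and still be on plan.** A reader might infer this from two targets in a trial with unblinded surgeons and analysts. The article permits no range and describes no interim look at outcomes. Open conduct alone does not show that results would guide the stopping point, and with 3-year DFS and about 3 years of enrolment, most patients would not have reached 3 years when accrual closes.
- **That the stated power depends on which total is used.** It does not: moving from 156 to 178 per arm adds about 3 percentage points, and both are far below 80%.
- **That 356 are to be screened and 312 randomized.** This would be a harmless explanation, but no screening failure rate is given and 356 is drawn directly from the per-arm requirement.

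It is also fair to say that the larger problem is the derivation of 156 itself. That is a separate matter, and whatever size is finally justified, the protocol needs one total.

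**Conclusion.** The point holds as an internal contradiction. Under 1:1 allocation 156 per arm gives 312, as the abstract says, and 356 is not reached from the stated figures by any route tried. The difference of 44 patients (14%) is exact. The 5 months is an illustration that rests on even accrual of 312 over exactly 36 months; the article says only about 3 years and does not say which total that covers.

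The consequence is an ambiguous recruitment target and study end date. Settling on 312 would make the article consistent but would not make the size adequate: at either total, power for a 0.07 difference is roughly a quarter before dropout, against the 80% stated.

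**What to change.** Check which number the ethics committees approved, then state one total and its matching per-arm figure in both the abstract and the sample size section, and record that recruitment stops there.

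- If 312 was approved, replace 356 with 312 (156 per arm) in the sample size section.
- If 356 was approved, print 178 per arm with its derivation and correct the abstract.

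Say plainly that this correction only reconciles the two totals. The claim of 80% power has to be restated separately, since neither total meets it under the stated inputs. The cost is one corrected number (with its per-arm counterpart if 356 stands) and a check against the approval; no change in conduct is needed unless sites have been working to the other target.
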